##### Handling of potential bias and heterogeneity across centres

Since there may be some heterogeneity in the practice of the research workers in identifying ATT needs across the different centres, between-centre heterogeneity will be explored in stratified analyses.

Because ATTILA is not a blinded study, it is conceivable that participants in the control group may be offered ATT by CASSR staff because they believe that risks to safety or independence might be better managed in this way, to delay or prevent institutionalisation. As a safeguard against such potential outcome bias, we will collect detailed data on ‘cross-overs’ in the control arm and reasons for this: in particular whether the cross-over is due to high risk incidents and the introduction of ATT is seen as an alternative to institutional care. To identify such potential outcome bias we will undertake sensitivity analyses, counting such participants as equivalent to meeting the primary outcome (i.e. equivalent to institutionalisation). However, the design of the study is pragmatic and the primary analysis will be restricted to actual cases of institutionalisations as awareness that the patient is, or is not, receiving these technologies will be just one of the complex factors that underlie institutionalisation.

##### Handling of missing data

Reasons for withdrawing from the study will be collected and, since stopping the ATTILA intervention is likely to be informative (e.g. a failure of or intolerance to the intervention), this information will be used in sensitivity analyses to investigate and reduce the impact of missing data.

##### Handling of reports of death

It is likely that a substantial number of deaths may occur amongst participants who have been previously institutionalised and therefore will have met the primary outcome. For deaths among participants resident in the community, deaths that occur as a consequence of an identified risk that the ATT might have affected will be included as a secondary outcome measure (documented as a serious adverse event) and the number of identified un-related deaths in the two study groups will be compared in the overall analysis and included in a sensitivity analysis of the primary outcomes.

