## Methods

### Design

ATTILA is a pragmatic randomised controlled trial over 104 weeks. Blinding will not be undertaken as it is not feasible. It will be conducted in the homes of people living with dementia and who are eligible to receive a package of social care through CASSRs. The trial will compare outcomes in two groups of participants randomised to one of two study arms: either (1) receiving an ATT needs assessment, followed by the installation of ATT devices and response services which will be deployed by the CASSR, or (2) receiving a semi-structured ATT needs assessment, followed by the installation of an ATT package restricted to only smoke and carbon monoxide detectors and a pendant alarm if indicated, also arranged by CASSRs. The key outcomes will be *time to institutionalisation* and *cost-effectiveness* of the intervention.

The trial is not funded to source, assess the need for or deploy ATT. Our approach is therefore to work alongside CASSRs that have been charged by the Department of Health with responsibility for establishing and developing local ATT services.

The study has been approved by the NHS Health Research Authority National Research Ethics Committee (REC reference number 12/LO/186) and is registered with the ISRCTN (http://www.controlled-trials.com/ISRCTN86537017).

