### Primary outcome measures

#### Time in days from randomisation to institutionalisation

This is defined as the permanent transition of the individual from living in their own home to nursing or residential care home or to admission to an acute care facility that results in permanent placement in a residential care or nursing home.

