### Statistics

#### Sample size calculation

On average, 50% of participants with a BADLS score of >15 will enter residential care after 24 months
[44]. A reduction in the estimated 24-month transition to care home rate by 30% (i.e. 50% institutionalised at 2 years reduced to 35%) would require the involvement of 500 participants allowing for 10% attrition due to death while still living in a community setting. This equates to an average of 55 days of longer independent home life for participants receiving ATT. The trial would therefore be powered to detect a mean institutional delay of a little less than 8 weeks. Expert opinion suggests that 8 weeks is close to the minimum clinically important difference in delaying institutionalisation
[45].

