#### Analyses

Statistical analysis will be by intention to treat (ITT). All participants who are randomised will be included in the comparison and analysed according to their randomised allocation, including those who discontinue the ATTILA study. Wherever possible, we will continue to collect follow-up data from these participants after they leave the study, so that the data set will be as complete as possible.

The primary outcome of time to institutionalisation will be analysed using standard log rank methods and will include all events, even those occurring after 2 years. Continuous outcome measures, e.g. health-related quality of life and functional ability measures, will be analysed using repeated measures regression techniques to maximise statistical power. Exploratory subgroup analyses will be undertaken, with appropriate caution, to investigate any influence of the baseline prognostic factors (gender, age, risk profile, support structure) on outcome.

For qualitative data, thematic analysis of transcripts and field notes will be undertaken to develop themes emerging inductively from data and narrative analysis of longitudinal elements to identify and contextualise acceptable and less-acceptable practices and features of AT equipment use. A collaborative analytic strategy will involve appropriate research team members and service user/carer researchers to enhance validity and to help integrate qualitative and quantitative findings. This component will be subject to a supplementary application for ethical review.

Local, site-specific reports will be produced by each local ATTILA research site towards the end of the fieldwork period. The timing of reports and locally specific content will be locally discussed and negotiated between the local PI and designated senior managers within the local CASSR.

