##### Competing risk analysis

At baseline, we will collect data on the categories of risk (e.g. safety within the home or wandering) and the recommended ATT intervention to protect against this risk. In cases where two types of technology are recommended that might both reduce a particular risk, we will undertake competing risk analyses to try to disentangle the relative efficacy of each intervention. We will enhance statistical power for such analyses by reviewing each institutionalised patient to classify the contribution of particular risk behaviours to the participant’s transition to institutional care.

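### The death sensitivity analysis of the primary outcome takes in only un-related community deaths and omits those ATT might have affected, so it cannot detect an exchange of placements for deaths at home

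*Protocol article*

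**What the plan says.** All references are to the protocol article.

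- **Event** (section Time in days from randomisation to institutionalisation). The article words it so: "This is defined as the permanent transition of the individual from living in their own home to nursing or residential care home". An acute admission that ends in such a placement also counts. Death is not part of it.
- **Test** (Analyses): the primary outcome "will be analysed using standard log rank methods and will include all events, even those occurring after 2 years". Under Handling of potential bias and heterogeneity across centres, "the primary analysis will be restricted to actual cases of institutionalisations".
- **Deaths in the community** (Handling of reports of death) are split in two. First, "deaths that occur as a consequence of an identified risk that the ATT might have affected will be included as a secondary outcome measure"; these are recorded as serious adverse events. Second, "the number of identified un-related deaths in the two study groups will be compared in the overall analysis and included in a sensitivity analysis"; that analysis concerns the primary outcomes.
- **Competing risks** (Competing risk analysis): where two technologies are recommended for the same risk, "we will undertake competing risk analyses to try to disentangle the relative efficacy of each intervention". Death before placement is not mentioned there.
- **Blinding** (Design): "Blinding will not be undertaken as it is not feasible".

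**The concern.** Death at home prevents later institutionalisation, so it is a competing event. In a log-rank test restricted to placements it can enter only as censoring. The article does not use that word, but no other handling fits the two sections on the primary analysis.

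A sensitivity analysis for death should ask whether the result survives once deaths are counted. Un-related deaths should be roughly balanced by randomisation, so adding them tests little. Deaths from a risk that ATT is meant to manage are the ones that treatment can move, and they are left out. Assigning a death to one class or the other is also a judgement made by people who may know the allocation.

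The aim is that people live at home independently and safely. Someone kept at home who then dies of the managed risk counts as never institutionalised in both analyses. Conversely, if ATT prevents such deaths, the extra control deaths count as non-events and can mask the benefit.

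A smaller matter is the section headed Competing risk analysis. Competing-risk methods separate types of event. They do not give the relative efficacy of two technologies that were aimed at one risk and not randomised against each other.

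**Working it through.** **The plan's own figure.** The sample size assumes "50% institutionalised at 2 years reduced to 35" per cent, with 10% attrition from death in the community. Alpha, power and allocation ratio are not stated. Assuming two-sided 5%, 90% power and 1:1 allocation, the two-proportion formula with pooled null variance gives

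n = [1.96·√(2·0.425·0.575) + 1.2816·√(0.5·0.5 + 0.35·0.65)]² / 0.15² ≈ 227 per arm, 454 in all.

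Then 454 × 1.1 ≈ 500 and 454 / 0.9 ≈ 505, so 500 reproduces. The plan therefore allows for about 50 community deaths (10% of 500). It gives no division of these into related and un-related.

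**Assumptions for the illustration.** 250 per arm and two years of follow-up. The placement hazard is −ln(0.5)/2 = 0.3466 per year (from the 50% figure). The un-related death hazard is 0.05 per year (assumed). Time to placement-or-death has the same distribution in both arms. In the ATT arm only, a fraction f of placements become risk-related deaths at home (assumed 10% or 20%). Un-related deaths enter the planned sensitivity analysis as events; the article does not say how they enter.

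**Expected counts.** Total exit hazard = 0.3966, so the share leaving home by two years is 1 − exp(−0.7932) = 0.5476.
- Placements, control: 250 × (0.3466/0.3966) × 0.5476 ≈ 119.6.
- Un-related deaths, each arm: 250 × (0.05/0.3966) × 0.5476 ≈ 17.3.
- Exchanged deaths, ATT arm: 119.6 × f ≈ 12 (f = 10%) or 24 (f = 20%).

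**Chance of a significant result favouring ATT.** P ≈ Φ(|ln HR|·√(d/4) − 1.96), where d is the number of events.

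| f | Analysis | HR | d | P |
|---|---|---|---|---|
| 10% | Primary | 0.90 | 227 | 12% |
| 10% | Adding un-related deaths | (0.3119 + 0.05)/0.3966 = 0.913 | 262 | 11% |
| 10% | All deaths | 1.00 | – | 2.5% |
| 20% | Primary | 0.80 | 215 | 37% |
| 20% | Adding un-related deaths | (0.2773 + 0.05)/0.3966 = 0.825 | 250 | 33% |
| 20% | All deaths | 1.00 | – | 2.5% |

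Simulated trials under the same assumptions agree. In the order primary, planned sensitivity and all deaths, they give about 11-12%, 10-11% and 2.3-2.7% at f = 10%, and about 36-37%, 32-33% and 2.2-2.9% at f = 20%.

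**A second parameterisation.** Here 60% leave home by two years (50% placed, 10% un-related death), and x% of ATT participants die at home of an affectable cause instead of being placed. With 2,000 simulations per scenario, x = 2 / 5 / 10 / 15% gives 5 / 12 / 39 / 71% for the primary analysis and 5 / 11 / 33 / 62% for the planned sensitivity analysis. Counting all deaths gives about 2.5-3% throughout.

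**Direction.** The set-up is symmetric. The same exchange in the control arm gives the same chances of a result favouring control.

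**The case against.** The strongest reply is that the harm is not hidden, and this stands. ATT-relevant deaths are a secondary outcome. Serious adverse events are too, and serious-risk incidents are a secondary objective. Under Case accountability, the monitoring committee reviews adverse-event data together with effectiveness data at least every six months. In the scenario above (about 12 v 0 or 24 v 0 risk-related deaths), a Fisher test on that secondary outcome is significant in 98% or 100% of simulated trials. The primary test favours ATT with no significant death signal in only 0.15% or 0%. That detection rate depends on there being no such deaths among controls; background deaths in both arms would weaken it. It also leaves uncorrected the analysis intended to show whether the primary result withstands deaths.

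A reader might infer that both analyses will show a benefit. The figures do not support this: even the two scenarios in the table give 11-37%. The split is assumed, and the bias can run either way.

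A reader might also object that a Kaplan-Meier percentage overstates institutionalisation when deaths compete. The article plans a log-rank test and proposes no such estimate, so this is not an error in the plan.

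It may be said that the handling of deaths belongs in the analysis plan. Much of it does, but the article itself states which deaths enter, and that rule is the point.

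On competing risks, the article says only that it will try to separate the technologies, and it will classify each placement by the risk behaviours behind it. Such a classification can describe why people were placed. It does not yield the relative efficacy of two technologies for one risk, and nothing here affects the primary conclusion.

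**Conclusion.** The point holds as a defect of one stated sensitivity analysis and should be fixed. As written, that analysis omits the deaths most open to a treatment effect and relies on an unblinded judgement of relatedness. It therefore barely corrects the error it should expose: at about 12 exchanged deaths the false-positive chance goes from 11-12% to 10-11%, and at about 24 from 36-37% to 32-33%. Counting every death returns it to about 2.5%.

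These sizes rest on an assumed number of exchanged deaths, an assumed un-related death rate, exponential times and 1:1 allocation. The documents supply none of these. The conclusion that related deaths are non-events in both analyses rests only on the text. The documents do not support saying that the trial would conceal harm, or that the primary log-rank test must be replaced.

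**What to change.** 1. Redefine the sensitivity analysis as time to institutionalisation or death from any cause before institutionalisation, counting every community death whatever its attribution.
2. Report the cumulative incidence of institutionalisation with death as a competing event, and cause-specific hazard ratios for institutionalisation and for death before it.
3. Keep ATT-relevant deaths as a secondary outcome and serious adverse event, as planned.
4. Label the two-technology competing-risk analysis as descriptive. Do not replace it with comparisons within recommended-technology groups presented as randomised. Recruitment/consent procedures places the ATT assessment after randomisation, and Assessments rules out pre-testing, so those groups may depend on allocation.

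The cost is revised wording, a little extra analysis and complete recording of death dates. The article does not say that death dates are collected, and it promises follow-up after leaving the study only where possible, so this needs confirming. The change should be settled before outcomes are compared by arm.

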##### Competing risk analysis

At baseline, we will collect data on the categories of risk (e.g. safety within the home or wandering) and the recommended ATT intervention to protect against this risk. In cases where two types of technology are recommended that might both reduce a particular risk, we will undertake competing risk analyses to try to disentangle the relative efficacy of each intervention. We will enhance statistical power for such analyses by reviewing each institutionalised patient to classify the contribution of particular risk behaviours to the participant’s transition to institutional care.

### Ethical considerations

There are important ethical issues to be considered in any research involving people who are living with a diagnosis of dementia.

#### Ethics and randomised controlled trial (RCT) design

Although there is some research evidence to suggest ATT may have benefits, most of this evidence is based on small-scale and qualitative studies. Whilst much of this evidence supports the use of assistive technologies in maintaining safety in some specific cases and situations, it is insufficient to support conclusions that effectiveness and utility of ATT have been established. For this reason, we consider that it is ethical to conduct a trial as we have proposed here, to provide more definitive evidence about the impact of ATT on the lives of people with dementia and their carers.

##### Seeking consent

We will assume that consent is not an ‘event’ but a process. We will therefore actively seek reaffirmed consent on all the occasions that we contact participants and seek their data.

##### Release of personal data by the CASSR

We will, depending on the wish of the CASSR, either agree to a data exchange protocol to allow for the exchange of personal data or introduce a simple protocol to the FACS assessment procedures in the CASSR over the recruitment period. Social work practitioners will ask newly referred, and eligible, people for their permission for their contact details to be released to us so that we can contact them.

##### Informed consent

It will be made clear to potential participants and their carers what taking part in the study will entail, that they are not obliged to take part in the trial and that the care that they will continue to receive from the NHS and local CASSR teams will not be adversely affected if they choose not to participate or wish to withdraw from the trial at any point.

##### Mental capacity

A diagnosis of dementia does not necessarily mean that the potential participant cannot consent to take part in the study and careful, but tactful checks will be made to establish their capacity to consent. When the person does not have capacity to consent, we will seek to identify someone known to the participant who would be prepared to act as the participant’s consultee, within the meaning of England’s Mental Capacity Act (2005).

##### Participant benefit

In practice, participants in studies of this kind benefit from taking part as involvement can produce positive effects. Our objective, however, is to produce evidence that will provide a robust basis for service development and will therefore benefit people living with dementia and their carers. The study team has the appropriate skills and experience in conducting clinical trials with people with dementia and includes those with specific expertise in the use and evaluation of ATT in dementia, statistics, health economics evaluation and social research methodologies. The team is distributed over a number of large population centres, which will enable the recruitment of the relatively high numbers of participants that the trial design requires. Large-scale clinical trials are expensive to conduct but are needed to provide the definitive answers that important clinical questions required so as to develop and implement clinically and cost-effective interventions within the NHS and CASSRs in England.

## Discussion

ATT is promoted by the Department of Health in England as a means of supporting older people at home. ATT is increasingly being offered as a mainstream service, and investment in this technology by CASSRs is increasing rapidly in the belief that it will save money. At present there is limited evidence to support this view. The only existing RCT evidence (from the WSD) did not specifically include people with dementia. The needs of this group mean that ATT will need to be deployed differently, and the impact of ATT may also be different compared to people without dementia. At a time of economic austerity, the provision of ATT may not, in fact, be cost-effective. If, however, ATT is shown to help people with dementia remain independent and improve their health-related quality of life, as well as being cost-effective, then investment in ATT will be fully justified.

## Trial status

In progress.

## Abbreviations

ATT: Assistive technology and telecare; CASSR: Councils with Adult Social Services Responsibilities; NHS: National Health Service; FACS: Fair Access to Care Services; RCT: Randomised controlled trial; WSD: Whole system demonstrator.
